## Discussion

The RECALL study aims to provide insight into the effects of rivastigmine on inter-ictal delirium, and to study the determinants and subtypes of cognitive side-effects of ECT in older persons. For this purpose, the design consists of a prospective cohort study in older patients treated with ECT for depression, primarily aiming to identify patients eligible for the cross-over trial to examine rivastigmine as a treatment for inter-ictal delirium. The prospective cohort is efficiently used to provide insight into cognitive side-effects and their determinants. We hypothesize that rivastigmine can prevent the excessive post-ECT drop in acetylcholine, and through this mechanism, reduce inter-ictal delirium severity. To our knowledge, the RECALL study will be the first clinical trial in patients with inter-ictal delirium during ECT.

The RECALL study will provide us with a large selection of putative determinants and outcome measures of ECT-related cognitive side-effects. Since these determinants are measured at baseline, their association with the onset of inter-ictal delirium can be assessed. Furthermore, the wide array of cognitive measures could enable detection of ECT-related cognitive side-effects. To date, studies on cognitive side-effects during ECT are often hampered by limited assessment of (putative predictors of) ECT-related cognitive side-effects. In addition, it enables detailed description of the study sample, facilitating generalizability of findings.

The cross-over design is chosen for three specific reasons; (1) to reduce the influence of confounding covariates, as each crossover patient serves as his or her own control; (2) to enable all trial patients to benefit from the study medication; and (3) most important, feasibility, as cross-over designs require fewer patients than non-cross-over designs to achieve sufficient power (71). The feasibility was the major argument for the design team as this is a population that is particularly hard to study. It is difficult to include patients due to less motivation which is a symptom of their disease, and—in case of legal incapability- doubts from the legal representative (e.g., family) to agree to an additional extensive battery of tests during the treatment. In addition, as in all studies on depression, we predict that the anhedonia and indecisiveness, core symptoms of depression, cause difficulties for patients to stay motivated during the entire study, resulting in missing data. The cross-over design allows this study to achieve sufficient power with 30 delirious patients completing the trial. A potential bias in cross-over designs may be “carry-over” effects. However, rivastigmine has a short elimination time [T1/2 patch = 3.4 h (72)], therefore a minimal “wash-out” period of 1 day is deemed sufficient. After removal of the patch, rivastigmine is eliminated for more than 99% within 24 h—or before the next ECT session is done. Furthermore, transdermal rivastigmine was chosen over other AChI due to reported superiority on gastro-intestinal side-effects and similar expected efficacy (73–75).

A limitation of our study is the possibly invalid use of the MMSE as an inclusion measure for patients with an inter-ictal delirium. It might be improper, as it is previously not validated as a tool for the diagnosis of inter-ictal delirium, or any other delirium (76). The same goes for the MMSE as a measure of delirium severity. However, we claim, based on our clinical experience, that inter-ictal delirium does not always behave as a “regular” delirium and therefore does not always meet the criteria for delirium as measured with the CAM. For example, hallucinations are often lacking, and the patients usually suffer from clouding of consciousness, persistent disorientation or reduced speed of processing. Hence, by screening for inter-ictal delirium using the CAM only, eligible patients for the trial might be missed.

In short, this paper provides the study protocol of the first clinical trial on interictal delirium, embedded in a cohort study that extensively measures ECT-related cognitive side-effects and their putative determinants. These extensive (outcome) measures facilitate future research, and may contribute to a future consensus on cognitive testing during ECT. Most importantly, this study may provide evidence for treatment of inter-ictal delirium with rivastigmine.

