### Study population and inclusion criteria

In- and outpatients, aged 55 years or older, fulfilling the Composite International Diagnostic Interview CIDI) criteria of a Major Depressive Episode—in the context of a unipolar major depressive disorder or bipolar disorder- and referred for ECT-treatment, are asked to participate in the cohort and, in case of occurrence of inter-ictal delirium, in the trial (22–24). Before inclusion, they provide a written informed consent form. The presence of an inter-ictal delirium is examined with the Confusion Assessment Method (25) (CAM) and/or Mini Mental State Examination (26) (MMSE), administered by a trained research assistant. For a diagnosis of inter-ictal delirium, patients need to have a CAM score indicating delirium or a drop in MMSE-score of at least 4 points as compared to baseline. The evaluation of inter-ictal delirium was done during regular screening once weekly, preferably in the middle of a week, 1 day (and maximum 2 days) after ECT. This timing was chosen to (1) select persistent cases of delirium, and hence not to include mild disorientation or transient delirious episodes immediately post-ECT; (2) to increase feasibility by avoiding cognitive testing during weekends and (3) to diminish the learning effect of repeated cognitive testing. Once delirium was diagnosed, an evaluation was done by the clinician to indicate whether it was needed to further exclude possible causes of delirium.

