### RECALL trial: Treatment allocation, intervention, and blinding

After inclusion in the trial, randomization is organized with a two by two Williams design (29). Block randomization is performed by the pharmacy department of the Amsterdam University Medical Center—location VUmc, with stratification for each site. Patients are randomly assigned to either the rivastigmine-followed-by-placebo group, or the placebo-followed-by-rivastigmine group. Each treatment arm lasts for four consecutive ECT sessions (Figure 1). Except for the unblinded nurse or research assistant (i.e., nurse or research assistant who is not involved in other parts of the study, nor in clinical practice, but only applies the patches), all other study members are blinded. “Trial treatment randomization lists” with codes are provided by an independent pharmacist and will only be available for the unblinded nurse or research assistant who applies the patches. Rivastigmine patches delivering 4.6 mg/24 h (Hexal AG, Holzkirchen, Germany) and Hansaplast® placebo patches (of similar size) are labeled in accordance with EU GMP annex 13 regulations and supplied to the sites. To improve and monitor adherence to the trial protocol, drug accountability lists are filled in. The Tmax of rivastigmine patches is 10–16 h, therefore the application of the rivastigmine (and placebo) patches is done the evening prior to ECT. The patch is removed after 24 h. As previously mentioned, during the trial, co-medication is allowed and there are no restrictions to clinical care as usual. As specified in the exclusion criteria however, patients with adjustments in antipsychotic medication or in electrode placement, are excluded from the trial. Benzodiazepines are allowed (e.g., in cases of profound agitation or insomnia). All changes in medications during the trial are registered after every ECT-session. Prior to each ECT-session, side-effects of rivastigmine are assessed, and in case of serious side-effects (e.g., gastrointestinal adverse reactions such as severe nausea), the participation in the trial will be stopped and rivastigmine discontinued. In case of persistent side-effect after discontinuation, the clinician will treat the patient according to the clinical picture (e.g., anti-emetics in case of nausea).

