*ATHF, Antidepressant Treatment History Form; BMI, Body Mass Index; SPPB, Short Physical Performance Battery; BAI, Beck Anxiety Inventory; GDS, Geriatric Depression Scale; AES, Apathy Evaluation Scale; MADRS, Montgomery Åsberg Depression Scale; IQCODE, Informant Questionnaire on Cognitive Decline in the Elderly; DRS-R-98, Delirium Rating Scale-Revised-98; MMSE, Mini-Mental State Examination; RASS, Richmond Agitation Sedation Scale; CAM, Confusion Assessment Method*.

∧ *The day of measurement is Wednesday, as ECT is done twice weekly*.

* *Physical activity includes assessment of mobility, International Physical Activity Questionnaire (IPAQ), and self-reported activities of daily living (ADL)*.

** *Stroop Color Word Test, 15-Words Test or Auditory Verbal Learning Test, Trail making Test, Kopelman Autobiographic Memory Interview, and Visual Association Test*.

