#### Primary outcome measure

During the trial, the effect of rivastigmine on inter-ictal delirium is examined through the Delirium Rating Scale-Revised-98 (DRS-R-98) (30). It was demonstrated that the DRS-R-98 is sensitive, specific, reliable, and easy to use for the assessment of severity of a delirium (30). We will compare delta-scores of the DRS-R-98 computed over the period of rivastigmine-use and placebo (T3-T0 and T6-T3, depending on whether the patients start with rivastigmine or placebo). This is assessed by a trained, blinded research nurse once weekly.

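### Drug half-life does not settle carry-over of the delirium state, and the planned T3-T0 versus T6-T3 contrast recovers the true effect only if that state persists in full

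*Protocol article*

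**What the plan says.** - **Wash-out (Discussion).** Carry-over is named as a possible bias of the cross-over design. The reply is pharmacokinetic: the patch half-life is 3.4 h, a wash-out "period of 1 day is deemed sufficient", and after patch removal "rivastigmine is eliminated for more than 99% within 24 h".
- **Patch timing (RECALL trial: Treatment allocation, intervention, and blinding).** Application of the "patches is done the evening prior to ECT", and "The patch is removed after 24 h", which puts removal on the evening of the ECT day.
- **Rating time (Table 1 under Outcome measures).** T3 is the day after the second trial ECT and T6 the day after the fourth. The footnote adds: "The day of measurement is Wednesday, as ECT is done twice weekly".
- **Primary contrast (Primary outcome measure).** Delta scores are compared between rivastigmine and placebo: "T3-T0 and T6-T3, depending on whether the patients start with rivastigmine or placebo".
- **Model (Data analysis).** Treatment is a within factor and sequence a between factor. Each period is two ECT sessions over 7 days. The treatment allocation section instead gives four sessions per arm.
- **Nature of the condition (Study population and inclusion criteria).** Screening is timed to "select persistent cases of delirium".

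**The concern.** The half-life describes the drug. The DRS-R-98 describes the delirium. At T3 and T6 the patch has been off since the previous evening, so the trial already looks for an effect that outlasts most of the drug. Elimination of the drug cannot then be the only evidence that no such effect remains later.

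The planned estimator adds to this. T3 closes period 1 and opens period 2. In patients who start on rivastigmine, any benefit at T3 lowers the baseline of the placebo period. If the benefit then fades, the return to the untreated level is scored as worsening under placebo and is added to the apparent benefit of rivastigmine. The size of the primary result therefore depends on how far the state persists, which the document does not address.

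**Working it through.** **1. The plan's own figure.** Drug left after h hours = 0.5^(h/3.4). At 24 h this is 0.75%, so 99.25% is eliminated. The statement of more than 99% reproduces.

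**2. Drug left at the rating.** The article gives no clock times. Assume removal between 18:00 and 22:00 and rating between 09:00 and 17:00 the next day, which is 11 to 23 h. Then 0.5^(11/3.4) = 10.6% and 0.5^(23/3.4) = 0.9%. The inclusion section allows its weekly assessment up to 2 days after ECT. At 36 h or more, less than 0.1% is left.

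**3. Model for the contrasts.** Let tau be the true effect (negative is improvement), L the share of it still present at T6 after a switch to placebo, and p0, p1, p2 the untreated means at T0, T3, T6. Assume equal numbers per sequence and the same tau in both periods.

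| Sequence | T0 | T3 | T6 |
|---|---|---|---|
| Rivastigmine first | p0 | p1 + tau | p2 + L·tau |
| Placebo first | p0 | p1 | p2 + tau |

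**4. Planned delta contrast (rivastigmine minus placebo).**
- Rivastigmine first: (T3-T0) - (T6-T3) = (2·p1 - p0 - p2) + tau(2 - L).
- Placebo first: (T6-T3) - (T3-T0) = -(2·p1 - p0 - p2) + tau.
- Average: tau(3 - L)/2 = tau(1.5 - L/2).

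**5. End-of-period contrast.**
- Rivastigmine first: T3-T6 = (p1 - p2) + tau(1 - L).
- Placebo first: T6-T3 = -(p1 - p2) + tau.
- Average: tau(1 - L/2).

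**6. First-period contrast.** T3 between sequences: (p1 + tau) - p1 = tau, whatever L is.

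**7. Numbers.** tau = -4 is the effect in the sample size section. L is not given, so its full range is shown.

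| L | Delta contrast | T3 versus T6 | First period |
|---|---|---|---|
| 0 | -6 | -4 | -4 |
| 0.5 | -5 | -3 | -4 |
| 1 | -4 | -2 | -4 |

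A simulation returned -5.98, -4.99 and -4.00 for the delta contrast and -3.99, -2.99 and -2.00 for T3 versus T6.

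**8. What the sequence factor shows.** Summed over both periods the deltas equal T6-T0. The difference between sequences is L·tau - tau = tau(L - 1), that is +4, +2 and 0 points at L = 0, 0.5 and 1. On deltas the term vanishes under full persistence and is largest under none. On the raw sum T3+T6, with 15 per sequence, SD 7 and r = 0.50, its power to detect carry-over is 7% at L = 0.5 and 15% at L = 1.

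**9. Precision of the first-period comparison.** With 15 per sequence, SD 7 and r = 0.50 between T0 and T3, SE = 7 × sqrt(1 - 0.50²) × sqrt(2/15) = 7 × 0.866 × 0.365 = 2.21. Multiplied by 2.05 (t, 27 df), the 95% half-width is about 4.5 points.

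**The case against.** The strongest reply is that an effect lasting to the next day need not last a week. The Discussion's hypothesis works session by session: rivastigmine is meant to blunt the fall in acetylcholine after each ECT, and the patch is timed for that. On the two-session reading, T6 comes a week and two further ECTs after T3, and the drug has been cleared before the next session. This stands in part. A next-day effect does not prove carry-over to T6, and L may be near 0. But the article gives no evidence on how fast the state fades, and L = 0 is where the planned delta contrast is furthest from the truth.

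It can also be said that the sequence factor already addresses carry-over. It is stated and it carries some information, but it does not correct the treatment estimate, and on deltas a null result is what full persistence would produce.

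A further reply is that sensitivity analyses belong in an analysis plan that is not shown. That is accepted. The point rests on reasoning and an estimator that the article itself states.

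Three stronger readings are tempting and are not supported:
- *The article claims to rule out carry-over.* It calls it a potential bias and the wash-out sufficient, no more.
- *Carry-over is present, or the wash-out is shown to be too short.* No passage gives the duration of any effect on delirium.
- *Carry-over dilutes the planned estimate below the truth.* For the stated delta contrast, persistence moves the estimate from -6 towards the true -4. Dilution below the truth belongs to a T3-versus-T6 contrast, which the article does not plan.

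**Conclusion.** The concern holds in this form: the half-life supports wash-out of the drug and leaves persistence of the delirium state as an untested assumption. The stated primary contrast estimates tau(1.5 - L/2). It is right only at L = 1 and overstates the effect by half at L = 0, the condition the Discussion defends. The end-of-period contrast, tau(1 - L/2), is right only at L = 0.

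This rests on equal sequences, a constant tau and a single persistence share L. The 1% to 11% of drug left also rests on assumed clock times, but the contrasts do not depend on it. If tau is zero, none of the contrasts shifts, so the problem concerns the size and interpretation of an effect, not the creation of one where there is none.

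**What to change.** - **Discussion.** Say that the half-life supports drug wash-out only, and that absence of carry-over of the delirium state is assumed.
- **Primary outcome measure and Data analysis.** Base the cross-over estimate on the end-of-period scores T3 and T6, with a period term, and state that it is conditional on no carry-over. Do not describe the delta estimate as valid under no carry-over.
- **Supportive analysis.** Report beside it the first-period comparison of T3 between sequences, adjusted for T0, with no pre-test choosing between the two.
- **Period length.** Reconcile four ECT sessions per arm (treatment allocation section) with two per period (Data analysis), because this sets the time over which any effect can fade.

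**Cost.** No new data: one reworded sentence, a changed primary contrast that should be fixed before outcomes are compared by treatment, and one extra analysis. With 30 completers, SD 7 for a single rating and r = 0.50 between any two ratings, the per-patient SD is 7.0 for T3-T6 and 7 × sqrt(6 - 6 × 0.50) = 12.1 for the difference in deltas. Power at L = 0, 0.5 and 1 is then 86%, 62% and 33% for the end-of-period contrast, against 74%, 59% and 41% for the deltas. The change costs power only if persistence is high. The first-period estimate is imprecise: around -4 its interval would run from about -8.5 to +0.5, so it cannot settle even the direction alone and is a supportive check only.

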## Ethics Statement

The studies involving human participants were reviewed and approved by Medical-Ethical Board of VU University Medical Center and the Central Committee on Research involving Human Subjects (CCMO). The patients/participants provided their written informed consent to participate in this study.

